### Clinical outcomes

The self-reported functional evaluation DASH and PRWE, visual analogue pain scale (VAS), radiographic measures, objective functional evaluation will be performed by independent evaluators at intervals provided in Table 1. For the outcomes at 8,12 and 24 weeks the evaluators will be blinded to the patient assignment groups. The minimum clinical follow-up will be 24 weeks, with the following parameters being considered to evaluate the results:

**Table 1 Tab1:** Outcomes and measurement time

	1 W	2 W	3 W	4 W	6 W	8 W	12 W	24 W
X rays	x	x	x	x	x	x	x	x
DASH		x			x	x	x	x
PRWE						x	x	x
VAS	x	x	x	x	x	x	x	x
AOM					x	x	x	x
Palmar Grip						x	x	x

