**Methods:**

This is a randomized clinical trial with parallel groups and a blinded evaluator. There are two non-surgical interventions: AE and BE. Patients will be randomly assigned. A hundred twenty eight consecutive adult patients with acute (up to 7 days) displaced DRF of type A2, A3, C1, C2 or C3 by the Arbeitsgemeinschaft für Osteosynthesefragen (AO) classification will be included. The primary outcome will be the maintenance of reduction by evaluation of radiographic parameters and Disabilities of the Arm, Shoulder and Hand Questionnaire (DASH). Secondary outcomes include function measured by Patient Rated Wrist Evaluation (PRWE), pain measured by the Visual Analogue Scale (VAS), objective functional evaluation (goniometry and dynamometry) and rate of complications. Evaluations will be performed at 1, 2, 3, 4, 6, 8, 12 and 24 weeks. For the Student’s t-test, a difference of 10 points in DASH score, with 95% confidence interval, a statistical power of 95%, and 20% sampling error. We consider an extra 10% for balancing follow up losses results in 64 patients per group.

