### Method for closed reduction and immobilization

The patient will be submitted to the closed reduction of the fracture through a traction and counter-traction technique. Materials needed for application of the two splinting techniques will be available in the operating room. Initially, all patients will receive a short radial splint that will be performed with a 20 cm wide gypsum cut to fit the thumb (Fig. 2a). The splint will be applied to the radial aspect of the wrist covering the volar and dorsal portion of the radius to the elbow. The splint will be moulded with three point fixation as described by Charnley [27]. The three points will be defined after a metal pointer will be placed beside the limb to identify the site of fracture by using the image intensification. Patients randomized to the above-elbow splint will receive a complementation of immobilization with a 15 cm width splint on the ulnar aspect of the forearm that begins at the middle of the forearm and extends into the armpit. The elbow will be immobilized at 90 degrees, and in a neutral position to block pronosupination (Fig. 2b). Cotton tubular mesh, cotton stripes and crepe bandage will be used in both bindings. Regardless of the immobilization adopted, all wrists will be positioned with slight flexion and ulnar deviation. Patients will be encouraged to actively move their fingers and the ipsilateral shoulder.

Patients with above-elbow immobilization will remain for 4 weeks with the splint followed by 2 weeks of below-elbow immobilization. The immobilization will be removed after 6 weeks.

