### Primary outcomes

#### Radiographic parameters

Maintenance of reduction by evaluation wrist radiographs in PA and lateral x-rays at the following intervals: one, two, three, four, six, eight, twelve and twenty-four weeks after fracture reduction.

The radial height, radial inclination, volar tilt, ulnar variance, intra-articular step off or gap and carpal alignment will be used to determine maintenance of reduction at every follow-up visit. Measurements will be made on the radiographs with a marker, straight edge, and protractor by two researchers independently on different occasions.

We will consider maintenance of reduction if:loss of reduction ≤2 mm in radial heightloss of reduction ≤4 degrees in radial inclinationdorsal angulation ≤10^o^≤ 2 mm intra-articular step offpositive ulnar variance ≤3 mmany carpal malalignment.

The contralateral side is used as a reference.

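### The trial is labelled evaluator-blinded without limit, but blinding is stated only for weeks 8, 12 and 24, leaving 5 of the 8 primary radiographic readings unprotected

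*Protocol article*

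**What the plan says.** The Methods paragraph of the abstract calls the study a "randomized clinical trial with parallel groups and a blinded evaluator", with no restriction to particular visits.

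The Clinical outcomes section assigns the assessments to independent evaluators throughout ("radiographic measures, objective functional evaluation will be performed by independent evaluators at intervals provided in Table 1") and then limits the blinding: "For the outcomes at 8,12 and 24 weeks the evaluators will be blinded to the patient assignment groups".

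Under Primary outcomes, Radiographic parameters, the films are taken at "one, two, three, four, six, eight, twelve and twenty-four weeks after fracture reduction", and maintenance of reduction is judged at each of those visits. The measurements are manual and are made "by two researchers independently on different occasions". That section says nothing about masking the readers.

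The section on closed reduction and immobilization gives every patient the same short radial splint. The above-elbow arm receives an additional ulnar splint that "begins at the middle of the forearm and extends into the armpit". That arm spends four weeks in the longer splint, "followed by 2 weeks of below-elbow immobilization". All immobilization ends after week 6.

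**The concern.** A reader of the abstract would take it that the radiographic primary outcome is assessed blind. The body of the article supports this only from week 8, when immobilization has already ended. The earlier films are the ones taken while the two treatments differ or are still in place, and the Discussion presents them as the means of finding loss of reduction early.

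Three features make reader expectation a plausible source of bias:

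- The Background states in advance that above-elbow immobilization is expected to hold the reduction better.
- The films are measured with marker, straight edge and protractor, and the Discussion concedes unmeasured tolerance limits.
- The measurements are compared with cut-offs of 2 mm, 3 mm, 4 degrees and 10 degrees, so a small shift near a cut-off changes the patient's classification.

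Two independent readers reduce random error. They do not remove an expectation that both share. Blinded films from week 8 onwards cannot fully repair an earlier call either. The Complications section indicates surgery once reduction is lost, so a later film may show an operated wrist.

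**Working it through.** **Step 1: compare the visit schedule with the blinding statement.** The visits come from Table 1 and the outcome sections; the blinded visits are those named under Clinical outcomes.

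| Outcome | Scheduled weeks | Outside the stated blinding | Would evaluator blinding protect it? |
|---|---|---|---|
| Radiographs (primary) | 1, 2, 3, 4, 6, 8, 12, 24 | 1, 2, 3, 4, 6 (5 of 8) | Yes, for the film reading |
| DASH (primary) | 2, 6, 8, 12, 24 | 2, 6 (2 of 5) | No, it is self-reported |
| VAS | all eight | 5 of 8 | No, it is self-reported |
| Arc of motion | 6, 8, 12, 24 | 6 (1 of 4) | Yes, where feasible |
| PRWE, grip strength | 8, 12, 24 | none | Already within the statement |

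The gap that evaluator blinding could close is therefore the five radiographic visits and, secondarily, week-6 goniometry.

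**Step 2: look for another provision that covers the five visits.** The section headed Randomization and masking deals with sequence generation and concealed envelopes only. Statistical methods blinds the statistical advisors, not the film readers. Clinical outcomes describes the evaluators as independent at every visit but as blinded only at three, so independence cannot be taken to mean blinding. Nothing else covers weeks 1 to 6.

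**Step 3: what an unblinded shift could do (illustration only).** The plan has no figure to reproduce here, and its sample size does not depend on this point. Assume that the loss of radial height is normal with mean 1.5 mm and SD 1.5 mm, and that there is no true difference between arms. These values are not in the article; the 2 mm cut-off is. If readings in one arm are shifted by d:

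P(loss > 2 mm) = 1 − Φ((2 − 1.5 − d) / 1.5)

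| Shift d (mm) | z | P(loss > 2 mm) | False difference |
|---|---|---|---|
| 0 | 0.333 | 0.369 | none |
| 0.1 | 0.267 | 0.395 | about 3 points |
| 0.25 | 0.167 | 0.434 | about 6 points |
| 0.5 | 0 | 0.500 | about 13 points |

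In an arm of 64, 13 points is about 8 patients (0.13 × 64 = 8.3). The result is driven by the assumed shift. It covers one criterion of six and supposes that both readers share the shift.

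**The case against.** The strongest reply is that the article is open about when blinding applies, so the abstract's label is shorthand, and that the stated comparison is at six months, where week 24 is covered. This carries some weight for the six-month analysis. It does not settle the matter, because the article itself makes maintenance of reduction a primary outcome judged at every visit, and because a call of lost reduction before week 8 can alter what the later films show.

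A reader might infer that the early films are read in knowledge of the arm. The article does not say so. Two researchers measuring independently on different occasions could be working away from the patient. What can be said is that the week 1 to 6 readings carry no stated protection. Nor does the article say that the single operator who applies all the splints is one of the two readers; it leaves this open.

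A reader might also infer that masking would be complete, because the added splint starts at mid-forearm and both arms are in below-elbow immobilization between weeks 4 and 6. That is a deduction. The above-elbow splint blocks forearm rotation and the below-elbow splint is not described as doing so, so forearm position on the film could hint at the arm.

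Finally, masking procedures are operational detail that an article may leave to the full protocol. That would answer a complaint of silence. Here the article names the blinded visits and leaves five out.

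**Conclusion.** The point stands in this form: the blinded-evaluator label is broader than the design described. Five of eight primary radiographic readings, made by hand against fixed cut-offs while the casts differ or are worn, are not protected by blinding. This part rests on the article's text alone and needs no assumption.

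The size of any resulting bias is unknown. The range of about 3 to 13 percentage points depends entirely on the assumed mean, SD and shift of 0.1 to 0.5 mm; the upper figure should not be quoted alone or as an estimate for this trial. The matter should be corrected, but it does not invalidate the blinded readings at weeks 8, 12 and 24, and it does not affect the sample size.

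**What to change.** For the trial outcome, have the same two researchers measure the films from all eight visits with patient identity and arm coded and the area proximal to the wrist masked. Keep this separate from the clinic reading used for care. Confirm that neither reader is the operator who applies the splints. Then extend the blinding statement to all radiographic visits and, where feasible, to week-6 goniometry.

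The cost is mainly handling. With 128 patients, the five visits now outside the statement amount to at most 128 × 5 = 640 sets of films to code and mask. No extra radiographs are needed, and the two readers measure these films anyway. A further reader is needed only if one of the two turns out to be the operator.

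The limits should be stated. Masking may be imperfect because forearm rotation can differ by arm. It does not blind the clinic decision on loss of reduction, and it does not protect the patient-reported DASH and VAS.

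If this is not done, limit the blinded-evaluator claim to weeks 8 to 24, in the abstract as well as the body, and describe the week 1 to 6 radiographic readings as unblinded. That costs only a change of wording.

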### Primary outcomes

#### Radiographic parameters

Maintenance of reduction by evaluation wrist radiographs in PA and lateral x-rays at the following intervals: one, two, three, four, six, eight, twelve and twenty-four weeks after fracture reduction.

The radial height, radial inclination, volar tilt, ulnar variance, intra-articular step off or gap and carpal alignment will be used to determine maintenance of reduction at every follow-up visit. Measurements will be made on the radiographs with a marker, straight edge, and protractor by two researchers independently on different occasions.

We will consider maintenance of reduction if:loss of reduction ≤2 mm in radial heightloss of reduction ≤4 degrees in radial inclinationdorsal angulation ≤10^o^≤ 2 mm intra-articular step offpositive ulnar variance ≤3 mmany carpal malalignment.

The contralateral side is used as a reference.

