### Inclusion criteria

Displaced and reducible fractures classified by AO as type A2, A3, C1, C2 and C3 will be included if one of these conditions is present.Radial height – loss >2 mm [15–19].Radial Inclination - loss >4° [17, 20, 21].Dorsal angulation >10^o^ [5, 18, 20].Positive ulnar variance – loss >3 mm [19–21].Intra-articular step off or gap – >2 mm [5, 19, 22].Carpal malalignment [19, 23].

The contralateral side is used as a reference.

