### Radiological measurements

The volar tilt, the radial inclination, the radial height, the ulnar variance and the intra-articular step off or gap were determined on posteroanterior (PA) and lateral (L) radiographs views obtained using a standardised procedure [24].

The standard method of obtaining a PA radiograph is with the shoulder in 90° of abduction, the elbow in 90° of flexion and the wrist in a neutral position. For the lateral view, the shoulder is adducted and the elbow is in 90° of flexion with the hand positioned in the same plane as the humerus [19].

The volar tilt, also called palmar tilt is measured on the lateral view and refers to the distance between a line through the dorsal and palmar boundary points of the radial joint surface and the perpendicular to the longitudinal axis of the radial shaft.

The radial inclination, also know as radial deviation is measured on the PA view and refers to the distance between a line through the radial and ulnar boundaries of the radial joint surface and the perpendicular to the longitudinal axis of the radial shaft.

The radial height, also called radial lenght is measured on the PA view and refers to the difference in axial direction of the radius between the distal tip of the radial styloid and the most distal aspect of the ulnar articular surface.

The ulnar variance, also called the radioulnar index is measured on the PA view and refers to the vertical distance between a line parallel to the medial corner of the articular surface of the radius and a line parallel to the most distal point of the articular surface of the ulnar head, both of which are perpendicular to the long axis of the radius.

The intra-articular step off or gap is measured on PA or lateral view and refers articular incongruity.

The carpal alignment is measured on lateral view. Two lines are drawn, one along the long axis of the capitate and other along the long axis of the radius. The lines do intersect within the carpus.

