#### Complications

Any clinical situation requiring treatment (clinical or surgical procedure) not provided in the protocol will be considered as a complication. All complications will be recorded for further stratification into major and minor complications.

In cases where there is loss of reduction, patients will be informed and surgical treatment indicated.

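### As written, the primary radiographic rule counts carpal malalignment towards maintained reduction and leaves out articular gap, contradicting the entry definition of displacement

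*Protocol article*

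**What the plan says.** Protocol article, Primary outcomes, Radiographic parameters: the determinants are named first, and they include gap and the carpus: "intra-articular step off or gap and carpal alignment will be used to determine maintenance of reduction". The rule then opens with "We will consider maintenance of reduction if" and lists its conditions. The last three, whose line breaks are lost in the text, are "intra-articular step offpositive ulnar variance ≤3 mmany carpal malalignment". The list does not say whether all conditions must hold.

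Inclusion criteria: a fracture qualifies as displaced if one listed condition is present. The list includes "Intra-articular step off or gap – >2 mm", "Positive ulnar variance – loss >3 mm" and "Carpal malalignment [19, 23".

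Radiological measurements: step off or gap is described as one measure of articular incongruity. Carpal alignment is judged from the capitate and radius axes: "The lines do intersect within the carpus".

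Complications: the failure side of the rule is also used outside the analysis: "In cases where there is loss of reduction, patients will be informed and surgical treatment indicated".

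Both the inclusion criteria and the outcome rule take the opposite wrist as reference.

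**The concern.** Every other item in the outcome list is a limit that a maintained wrist must not exceed. The carpal item is an abnormality, placed in a list that defines success. It contradicts the inclusion criteria, and also the outcome section's own statement that carpal alignment helps to determine maintenance. The articular item drops a component that the inclusion criteria, the measurement section and the preceding paragraph of the outcome section all name.

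Maintenance of reduction is one of two named primary outcomes, alongside DASH, and the hypothesis that above-elbow immobilization does better concerns loss of reduction and radiographic parameters. A yes/no rule for that outcome should give one answer for each set of measurements, and the answer should agree with what the trial calls displaced at entry.

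**Working it through.** No calculated figure in the article rests on this rule. The only one is the DASH sample size: 2 × (1.960 + 1.645)² × (15/10)² = 58.5, or 59 per group against 58 stated. It has no bearing on this point.

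**Item by item**

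| Item | Displaced at entry | Maintained at follow-up | Complement? |
|---|---|---|---|
| Radial height | loss >2 mm | loss ≤2 mm | yes |
| Radial inclination | loss >4° | loss ≤4° | yes |
| Dorsal angulation | >10° | ≤10° | yes |
| Articular step off | >2 mm | ≤2 mm | yes |
| Articular gap | >2 mm | not listed | **no** |
| Ulnar variance | loss >3 mm | ≤3 mm, without the word loss | wording differs |
| Carpus | malalignment | any malalignment | **no** |

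Four thresholds are exact complements. That is evidence that the complement was intended and that the two departures are errors, not a deliberate second definition.

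**Enumeration.** Treat each of the seven items as abnormal or not, which gives 2⁷ = 128 patterns. At entry a pattern is displaced if at least one item is abnormal (127 patterns; 1 is not). Ulnar variance is taken as matching, and maintenance is taken to require every listed condition, which the article does not say. A conflict is a pattern that is both displaced and maintained, or neither.

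- *Malalignment required for success.* Maintained: malalignment alone; malalignment plus gap. Both are displaced at entry. The wholly normal wrist is not maintained. Conflicts: 2 + 1 = 3.
- *Malalignment tolerated.* Maintained: the normal wrist; gap alone; malalignment alone; both. The last three are displaced at entry. Conflicts: 3. Carpal alignment then determines nothing, contrary to the section's own statement.
- *The carpal word corrected from any to no, nothing else changed.* Maintained: the normal wrist; gap alone. Conflicts: 1.
- *Carpal item corrected and gap added.* Maintained: the normal wrist only. Conflicts: 0.

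**What tolerating these findings would do, under assumed rates.** The article gives no loss rates. Suppose true loss is 15% v 30% with 58 per group, and a fraction f of losses, equal in both arms, shows only as malalignment or gap. The observed difference is 15 × (1 − f) points. Power of the two-sided 5% test is Φ{[d√n − 1.96√(2p̄(1 − p̄))] / √(p₁(1 − p₁) + p₂(1 − p₂))}, where p₁ and p₂ are the observed loss rates, d their difference and p̄ their mean.

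| f | Difference (points) | Power |
|---|---|---|
| 0 | 15.0 | 49% |
| 10% | 13.5 | 44% |
| 20% | 12.0 | 39% |
| 30% | 10.5 | 34% |

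With 20% v 40%, power runs from 66% through 59% and 52% to 46%. The risk ratio does not move: at f = 20%, 24%/12% = 2, the same as 30%/15%.

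**The case against.** The strongest reply is that *any* is a plain slip for *no*. The inclusion criteria, the measurement section and the determinants paragraph leave one sensible meaning, and no assessor would call a well-aligned wrist a failure for being aligned. This is probably right. It explains the carpal item but does not repair the stated rule, and it does not bring gap back. For gap, the reply is that step off is shorthand for the combined parameter named just before the list. That is plausible, but the cut-off as written does not say so.

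Three stronger readings are tempting and not supported.

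- *That wrists are being misclassified.* The article cannot show whether assessors apply the text literally, or how many wrists have the findings concerned. That three of the five included AO types (C1 to C3) are intra-articular counts categories, not patients.
- *That the comparison is pulled towards no difference.* This holds for the risk difference under the tolerated reading with equal shares in both arms, as in the illustration. If malalignment were required for success, the contrast could shrink, vanish or reverse, depending on malalignment by arm.
- *That ulnar variance is a third contradiction.* A wrist at +3.5 mm against +2.0 mm on the other side (assumed values) has a difference of 1.5 mm, yet would fail if 3 mm were an absolute limit. But both sections name the opposite wrist as reference, so the natural reading is a difference. Only a clarity note remains.

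It is also fair that DASH is co-primary and alone drives the sample size, and that the radiographic measurements are collected whatever the rule says. This makes the fault recoverable; it does not make the rule correct.

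**Conclusion.** The point holds as an internal contradiction in a primary outcome definition. The carpal item is wrong as written under either literal reading, and the articular cut-off omits gap. Its size in logical terms is 3 conflicting patterns of 128 under either literal reading, 1 if only the carpal word is corrected, and 0 after the full correction. These are unweighted counts and say nothing about frequency. They assume that all conditions must hold and that ulnar variance is read against the opposite wrist. Neither the number of wrists affected nor the direction of any bias can be derived from the article. This is not detail left to an analysis plan: the article states the rule and states it wrongly.

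**What to change.** Restrict the change to the outcome definition in the Radiographic parameters section, and make it the complement of the inclusion criteria:

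- replace the carpal item with the absence of carpal malalignment, pointing to the description in Radiological measurements;
- extend the articular item to step off or gap of at most 2 mm;
- state that maintenance requires all conditions;
- as a clarity note, word ulnar variance as in the inclusion criteria, as a loss relative to the opposite wrist.

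Reclassify any films already scored from the recorded measurements. The cost is a wording change and, where needed, a rescoring pass. No new data are called for, because the protocol already has these parameters assessed at every follow-up visit; rescoring assumes that the values were kept and not only the yes/no result.

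The Complications section uses loss of reduction as a trigger for care, so the sponsor must reconcile it with the inclusion criteria and the corrected outcome rule. No position is taken here on care.
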